#### Cisgender women

- Pregnant and has established prenatal care, i.e., a prenatal care visit
- Scheduled for a different visit type in Epic (e.g., Gyn problem visit for heavy bleeding)
- Non-English or non-Spanish speaking
- HIV-infected
- Unable or unwilling to complete the Electronic Sexual History Form (eSHxForm)

#### Staff

- Unwilling to participate in feedback sessions

## **6. STUDY PRODUCT/INTERVENTION(S)**

### **6.1 Electronic Sexual History Form (eSHxForm):**

Ideally, all patients would complete the eSHxForm before the clinic visit. Currently, patients are asked to complete a paper medical history form upon arrival to the clinics (JH Gyn New Patient Questionnaire 5/16, **Appendix A**). This form has detailed sexual history questions (e.g., type of sex [anal, vaginal, oral], sexual orientation, number of partners, number of new partners, prior STIs). We plan to transform the paper version into an electronic form. We will add a point value to each sexual history question and program Epic to summarize the score behind the scenes. Based on the score, different messages will be shown to the patient (**Appendix C**). The score will be visible in the EHR but it will not have a label assigned. In other words, there will not be any stigmatizing language (e.g., high HIV risk) attached to the score. The scoring algorithm is based on our other published research. We will refer to this scored sexual health section as a Gyn HIV Risk Tool. Clinics will send the eSHxForm to patients to complete before the clinic visit. Messages will be sent via MyChart, email, or secure text messaging, per current clinical guidance. In the event that patients do not complete the eSHxForm before clinic, then they will receive a computer tablet upon arriving to their visit for completion while waiting for the provider.

Based on our experience with a different Gyn clinic-based project among our gyn cancer patients that used an electronic history form, approximately 65% of patients completed the pre-visit documentation. The remainder were asked to complete it on their own using clinic tablets while they waited for the provider. A small minority (<5%) were unable to complete the questionnaire and required the assistance of clinic staff. We will ask our medical assistants to assist the patient, but if she is unable to complete the eSHxForm, then the patient will not be included. Whether patients will respond differently to the eSHxForm, including the Gyn Risk Tool section depending on how it is administered or whether this will affect PrEP uptake is unknown. As part of our exploratory analysis, we will examine whether the mode of administration is related to responses to the Gyn HIV Risk Tool. In a sensitivity analysis for our primary outcome, we will also examine whether our results are robust to the administration mode, excluding those who used the less common modes.

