## 4. STUDY DESIGN

This is a Hybrid Type II effectiveness-implementation trial. A type II trial was selected because we are simultaneously testing the effectiveness of our intervention and implementation strategy. In other words, we are testing an implementation strategy during an effectiveness trial.

There are a few pre-trial procedures that will take place in **Phase I** including the following:

(1) **Motivational interviewing**: ObGyn provider training will be led by co-investigator [name]. [name] [name], has been invited as a speaker at the Gynecology and Obstetrics Department Grand Rounds to provide one 45-50-minute training for the department. Her scheduled date is September 29, 2022.

(2) **Creation of the electronic sexual history form (eSHxForm) that contains the Gyn HIV Risk Tool**: Currently, patients who have enrolled in MyChart, which is the patient portal for Epic, are sent a "Patient Reported History" questionnaire. These questionnaires are systems-wide and tailored to the department. Additionally, some divisions have developed secondary questionnaires that are specific to their clinical care needs, which are sent to patients before the clinic visit. As part of this research project, we will create a secondary questionnaire using the sexual health portion of our current paper history form (JH GYN NPQ A (05/16) **Appendix A**). We will add four additional sexual history questions from our Epic Risk Assessment Flowsheet (**Appendix B**).

(3) **EHR changes**: (a) The new eSHxForm will be integrated into the EHR after approval from the MyChart Committee. We have met with the chair to discuss our protocol and the changes are feasible; (b) We will add a point value to each sexual history question and program Epic to summarize the score behind the scenes. Based on the score, different messages will be shown to the patient (**Appendix C**). The score will not be visible in the EHR but part of the metadata on the backend. Scoring is done for several questionnaires already and will not be problematic; (c) We will edit our current provider EHR alert (**Appendix B**) to report their patients' HIV risk assessment level (based on how patients answer the sexual health questions above) and ask if the provider would like to discuss PrEP and add the required laboratory tests before starting PrEP.

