(4) **Staff training**: During scheduled staff meetings, group huddles, or individual meetings, we will discuss the eSHxForm workflow with nurses, clinic managers, front desk staff, medical assistants, and other relevant clinical staff. This will allow us to troubleshoot any anticipated problems. Patients are sent a clinic reminder text message before clinic visits. Staff will encourage patients to complete the MyChart questionnaires (general history and the secondary eSHxForm) called the "eCheck-in". This best practice is being used at some clinical sites within Obgyn already but not all.

(5) **Pilot testing**: We will pilot test the eSHxForm workflow at each clinical site to determine the most effective strategies to get patient participation before the clinic visit.

After the pre-trial procedures, enrolled providers (N=42) will be randomly assigned 1:1:1 to a study arm mentioned below.

**Phase II** includes conducting the clinical trial. Patients of the enrolled provider who attend the ObGyn clinic for any preventative visit will complete an electronic sexual history form (eSHxForm) before engaging the provider. Ideally, patients will complete the eSHxForm before clinic through a message sent through the patient portal (MyChart), email, or secure text messaging. If this has not been completed, then a computer tablet will be used while the patient waits for their provider.

Patients who score low (0-3) will receive an electronic message offering a laboratory HIV test per USPSTF guidelines, only if Epic does not locate an HIV test in the record already. USPSTF recommends those 15-65 receive at least one HIV test in their lifetime. If she accepts, then an EHR alert will pop-up for the clinic staff to pend the HIV test order for the provider to discuss with the patient and discuss. The clinic staff will notify each provider when there is an HIV test order pending in the chart. Based on our preliminary data, we anticipate that the majority of our patients will fall into this category of low risk (>90-95%).

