Patients who score medium or high (4-10) will be assigned a study arm based on their provider's group. This will occur automatically via programming integrated into the EHR based on the provider and the type of scheduled visit. The score will be recorded in EHR but it will not be labeled, i.e. a number will be there but nothing about HIV or risk of HIV. This medium/high score group is whom we consider **PrEP-eligible** (e.g., *at substantial HIV risk*) and is the focus of this implementation science study. Based on our preliminary data, we anticipate that a minority of patients (5-10%) will fall into these categories of medium or high risk.

**Clinical trial arms.** The Interventions are guided by the Information-Motivation-Behavior model of behavior change (**Figure 1**).

-Arm 1 Control: standard of care

-Arm 2 Patient-level intervention: patients will be shown a 2.5-minute PrEP animation (information) and their personalized HIV risk messaging (motivation)

-Arm 3 Patient and Provider multi-level intervention: patients will be shown a 2.5-minute PrEP animation (information) and their personalized HIV risk messaging (motivation) AND providers will receive an EHR alert about their patient's personalized HIV risk messaging and a recommendation to offer PrEP. The alert will allow the provider to accept to add the required laboratory tests to start PrEP or decline altogether. Orders will have to be signed by providers but the correct laboratory tests will be ordered to save time and ensure accuracy.

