There is no difference between Arms 2 and 3 regarding information and motivation. The difference between these two arms is the provider activity. We are trying to tease apart a clinic-based intervention that targets patients alone (Arm 2) versus both patients and providers (Arm 3). The primary outcome (behavior) is PrEP uptake, and this will be compared based on the Arm the patient is assigned, as is discussed in the data analysis plan. As competing interests (e.g., lack of time) and difficulty assessing the patient's HIV risk consistently have been listed as provider-level barriers to PrEP uptake; and patients do not perceive themselves to be at-risk of HIV, having these two arms will give us a lot of information about how to increase PrEP in women. For instance, Arm 2 will determine whether patients' awareness of their HIV risk will prompt them to ask their provider about PrEP or increase their desire to start PrEP; while Arm 3 will add an additional PrEP facilitator and determine if providers' awareness of their patients' HIV risk level will prompt them to discuss PrEP or increase PrEP uptake by patients.

**Figure 2. Study Schema.** There are two phases in the project. The first is to prepare documents, train staff, enroll providers and clinics. The second includes the clinical trial.

[figure not shown]

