## **6.3 PrEP videos**

Our research group developed patient (video clip [here](#)) and provider (video clip [here](#)) animations about PrEP. The videos were informed by patients and providers, and peer-reviewed. The Hopkins' pharmacy lead and patient education director reviewed the videos and approved them for clinical use. The videos are available in Epic under the Hopkins Program Library. The provider will view the provider animation during their training and the patient will be able to view the animation via a hyperlink embedded in the eSHxForm.

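### The protocol says both that the risk score is hidden in the EHR and that it is visible there; if it is built visible, Arm 1 and Arm 2 providers could receive part of what Arm 3 is meant to test

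*Protocol*

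**What the plan says.** The Protocol describes the display of the risk score three times.

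- Section 4, pre-trial item (3) on EHR changes: "The score will not be visible in the EHR but part of the metadata on the backend".
- Section 4, in the paragraph on medium and high scorers: "The score will be recorded in EHR but it will not be labeled, i.e. a number will be there".
- Section 6.1: "The score will be visible in the EHR but it will not have a label assigned".

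On the arms, section 4 gives the PrEP animation and personalized risk messaging to Arms 2 and 3, and adds a provider alert with a PrEP recommendation and ready-made laboratory orders in Arm 3. Of Arms 2 and 3 it says: "The difference between these two arms is the provider activity". It goes on to say that Arm 3 will show whether a provider's awareness of the patient's risk level leads to PrEP discussion or uptake. Section 3.1.1 makes the patient-only versus patient-plus-provider comparison the primary intervention objective.

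On delivery to patients, section 6.3 says that "the patient will be able to view the animation via a hyperlink embedded in the eSHxForm", and section 6.1 says: "Based on the score, different messages will be shown to the patient". Neither sentence mentions the arm. Eligible patients of every enrolled provider complete the form.

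**The concern.** The statements on visibility cannot both be configured in Epic, and the protocol does not say which one governs. If the build follows section 6.1, providers in Arms 1 and 2 will have in the chart a number that summarizes the patient's risk. Arm 3 is meant to differ from Arm 2 in what the provider knows and does, so part of the tested ingredient would then be present in the comparator arms.

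The effect would be to pull Arm 3 versus Arm 1 and Arm 3 versus Arm 2 toward no difference. The planned mixed model in section 8.5 compares patients by their provider's assigned arm and has no means of recovering a contrast that was diluted at delivery. Table 1 lists no measure of whether a provider saw the score, so the dilution might also go unnoticed. Section 5.1 explains the choice of providers as the randomized unit by the wish to limit contamination between arms, so the investigators already regard it as a threat.

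**Working it through.** **Step 1: the statements side by side.**

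| Place | Visible to chart users? | Label? |
|---|---|---|
| Section 4, item (3) | No, backend only | Not applicable |
| Section 4, medium/high scorers | A number is present | No |
| Section 6.1 | Yes | No |

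All three are current design text. The first contradicts the other two.

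**Step 2: which contrasts the score can reach.** A visible score would be open to providers in Arms 1 and 2 alike. Arm 3 versus Arm 1 and Arm 3 versus Arm 2 are therefore exposed. Arm 2 versus Arm 1 is not clearly affected, because both would receive the same number.

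**Step 3: how readable an unlabelled number is.** Section 6.1 gives avoidance of stigmatizing language as the reason for the missing label; it does not present it as concealment. Providers in every arm consent to the trial and view a PrEP animation (sections 7.1 and 13.5.1), and they know their own arm (section 8.4). The form's disclaimer in section 13.5.2.1 tells patients, without an arm condition, that the provider may receive the information. Some inference from the number is plausible. The documents do not show how much.

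**Step 4: the plan's own power figure.** Inputs from section 8.3: 1,170 patients, three arms, design effect 1 + (28 − 1) × 0.01 = 1.27, uptake 6% versus 15%, stated power 80%. Alpha is not stated there; two-sided 0.05 is assumed.

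- Effective n per arm = 1,170 / 3 / 1.27 = 307.1.
- Power = Φ{[Δ − 1.96 √(2p̄(1 − p̄)/n)] / √([p1(1 − p1) + p2(1 − p2)]/n)}.
- With p1 = 0.06, p2 = 0.15, p̄ = 0.105: (0.09 − 1.96 × 0.02474) / 0.02447 = 1.70, so power is 95.5%.

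The stated 80% does not reproduce. Alpha of 0.025 gives 92.1% and 0.0167 gives 89.6%; using one year's 390 patients as the total gives 55.6%. That is a separate matter and the present point does not depend on it.

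**Step 5: illustration of dilution.** Let c be the share of comparator patients who respond as Arm 3 patients would. The comparator rate becomes 6% + c × 9 points, and the expected difference becomes (1 − c) × 9 points. The value of c is an assumption throughout.

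| c | Comparator rate | Difference (points) | Power, two-sided 0.05 |
|---|---|---|---|
| 0 | 6.0% | 9.0 | 95.5% |
| 10% | 6.9% | 8.1 | 89.7% |
| 20% | 7.8% | 7.2 | 80.3% |
| 30% | 8.7% | 6.3 | 67.6% |
| 40% | 9.6% | 5.4 | 53.1% |
| 50% | 10.5% | 4.5 | 38.6% |

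At alpha 0.0167 the first and third rows become 89.6% and 66.1%.

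**Step 6: the animation link and messages.** Sections 6.1 and 6.3 state no arm condition. Section 4 does: it lists the animation and personalized message only under Arms 2 and 3, with assignment made by EHR programming according to the provider. Read together, this is a display condition left unstated in the two sections that define the intervention.

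**The case against.** The strongest reply is that an unlabelled number is a weak exposure. The Arm 3 alert actively describes the risk level, recommends PrEP and prepares the orders; a passive number does none of this. Much of the scored content comes from the existing history form and routine history-taking (sections 6.1 and 13.1.3), so providers in all arms may already have it. This stands as a limit on size. It does not remove the contradiction, and a ready-made total is still more than the separate answers.

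Second, on the plan's own rates a 20% leakage leaves power at 80.3%, about what section 8.3 claims. That is true, but nothing in section 8.3 reserves the surplus for contamination, and the expected difference still shrinks from 9 to 7.2 points whatever the power.

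Third, two of the three statements favour visibility, and nothing shows which was intended. This also stands. The case for the backend-only statement rests on keeping the arms apart.

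A reader might infer more than the text supports:

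- That providers know the cut-off of 4. No section says they are taught the scoring or its threshold.
- That Arm 1 patients will receive the animation. Section 4 restricts it to Arms 2 and 3, and a link inside the form is compatible with a screen shown only in those arms. Any such leakage could reach only Arm 1, since Arm 2 receives the animation by design, and Table 1 records viewing.
- That all score-based messages should be limited to Arms 2 and 3. Under section 4, low scorers with no HIV test on record are offered one without any arm condition, so such a limit would contradict the design.

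**Conclusion.** The contradiction on score visibility is certain and concerns part of what separates Arm 3 from the other arms. If the score is built visible, Arm 3 versus Arm 1 and Arm 3 versus Arm 2 could be diluted toward no difference. That this will happen, or by how much, cannot be established from the documents. The fall from 95.5% to 80.3% is an illustration resting on an assumed 20% leakage, an assumed two-sided 0.05, and the plan's 6%, 15% and 1.27.

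A steeper loss is easy to produce by assuming a smaller gap: 8% versus 15% goes from 77.7% to 56.4% at 20% leakage of that gap. The 8% appears nowhere in the protocol, which gives no Arm 2 rate distinct from Arm 3, so those figures should not be cited as the size of the problem.

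The missing arm condition on the animation link and risk message is a minor clarification.

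**What to change.** Reconcile the three statements by adopting the wording of section 4, item (3). The score is stored as backend metadata, appears in no provider- or staff-facing view in Arms 1 and 2, and risk information reaches providers only through the Arm 3 alert. Amend the later section 4 paragraph on medium and high scorers, and section 6.1, to match.

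As a clarification, state in sections 6.1 and 6.3 that the animation link and the personalized risk message for medium and high scorers appear only in Arms 2 and 3, as section 4 already intends. Leave the HIV-test message for low scorers unchanged in all arms.

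The cost is protocol wording and an Epic display setting, settled before go-live. No additional patients or data are needed.

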## **6.2 Epic Best Practice Alerts (BPAs)**

### **6.2.1 Medical assistant or other clinic staff BPA.**

We will create a BPA that will be displayed in Epic only if patients who scored low on the eSHxForm desire an HIV test. The BPA will allow the medical assistant to notify the provider of the patient's desire for HIV testing and that an order has been pended in Epic for their signature, after routine HIV counseling (see **Appendix B** for example).

### **6.2.2 Obgyn Provider BPA.**

As part of a previous PrEP project in the ObGyn clinics, we developed and implemented BPAs to assist providers with the identification of patients who may be PrEP eligible. The BPAs were displayed when a provider placed an antibiotic order PLUS the patient tested positive for a sexually transmitted infection. The alerts were well received by providers and led to increased PrEP discussions during its implementation. We will relaunch these BPAs as part of the 3rd Arm (multilevel intervention arm). The alert will include a description of the patient's HIV risk level based on how patients answer the sexual health questions) and a decision aid (ask if the provider would like to discuss PrEP and add the required laboratory tests before starting PrEP (see **Appendix B** for example).

## **6.3 PrEP videos**

Our research group developed patient (video clip [here](#)) and provider (video clip [here](#)) animations about PrEP. The videos were informed by patients and providers, and peer-reviewed. The Hopkins' pharmacy lead and patient education director reviewed the videos and approved them for clinical use. The videos are available in Epic under the Hopkins Program Library. The provider will view the provider animation during their training and the patient will be able to view the animation via a hyperlink embedded in the eSHxForm.

## **7. STUDY PROCEDURES**

### **7.1 ObGyn Providers:**

- 7.1.1 Recruitment will be via email, flyers (print and electronic), and word of mouth. Providers will not be recruited nor consented by a direct supervisor. Providers responding to an email or flyer will discuss the study with a research coordinator, who is not a direct supervisor. Recruitment will take place during providers meetings, before scheduled educational sessions, during scheduled work breaks, and other routine gatherings of providers.
- 7.1.2 Written informed consent will be obtained. Informed consent will be done by an interactive question and answer process where the potential subject will be asked specific questions to determine her understanding of the purpose, procedures, risks and benefits in participating in the study.
- 7.1.2 Motivational interview techniques will be presented as a Grand Rounds presentation for the entire department on September 29, 2022. Co-investigator from the University of Michigan will lead these efforts. Grand Rounds presentations are video recorded and can be viewed afterward. Also, brief (<25 minutes) online training modules will be created by our co-investigator for the participating ObGyn providers. The online module will test comprehension and basic skills (some sample questions will

include: identifying open-ended vs. closed-ended questions; understanding MI-consistent strategies; using rating scales to assess motivation, readiness, and confidence, etc.) We do not expect anyone to become an expert in motivational interviewing, however, the principles and basic skills can be taught briefly. Additionally, providers will be encouraged to view additional online modules quarterly. Immediate goals after viewing the training will be for providers to identify and understand the processes for implementing MI in their patient interactions (e.g., reflective statements), developing discrepancy, rolling with resistance, exploring ambivalence. Providers will learn how to avoid “MI traps” and how to implement communication strategies to help promote sexual health behavior change.

7.1.3 PrEP animations will be required to view. The 2 ½ minute animation will be sent to providers based on their preference. The animation provides brief educational material about PrEP.

7.1.4 Semi-structured in-depth interviews to evaluate the project (e.g., mainly processes) will occur throughout the project until we obtain feedback from 10-12 providers. We are not interested in the providers themselves for this qualitative portion and will not collect any of their PHI as part of these in-depth interviews.

